### Recruitment

The aim of the PELVIC study is to implement a clinical pathway by educating and stimulating local clinicians. Besides the targeted visits in the wash-in phase, no specific efforts will be made to achieve adequate participant enrolment.

### Allocation and blinding

Randomisation and allocation of the participating centres will be performed by the lead researcher using R statistics software. The randomisation sequence is unknown to all participating centres and clinicians, and centres were informed in a timely manner about the moment to switch to intervention by the lead researcher of this study. Although there is allocation concealment, this study is otherwise an open-label trial since subjects and physicians are aware of the assigned treatment (current practice vs clinical pathway).

### Data management and monitoring

Any information collected during this study will be encoded and stored in a password-protected database with restricted access to the researcher team only. Data will be entered once. The quality of the entered data will be monitored by checking entry for a random sample of patients prior to database locking. There will be no data safety monitoring board. This study does not introduce an investigational product or experimental intervention so no additional safety reporting will be performed.

### Statistical methods

Outcomes of all patients with an FFP will be analysed before and after the implementation of the clinical pathway. Patients will be assigned to current practice or clinical pathway cohort based on the date of first hospital contact (eg, emergency room visit, outpatient clinic visit, hospital admission date). When patients are diagnosed in a ‘clinical pathway’ centre but transferred to a pelvic expertise centre for fixation that is still in current practice, the patient will be assigned to the clinical pathway cohort. Data will be analysed by using the SPSS V.24.0 or higher (SPSS. Normality of continuous data will be tested with the Shapiro-Wilk test. Homogeneity of variances will be tested using the Levene’s test. A two-sided p<0.05 will be taken as threshold of statistical significance in all statistical tests. Primary analysis will be performed with an intention-to-treat analysis according to the randomisation order and cross-over dates. If implementation is not performed as scheduled, secondary analysis will be performed according to a per-protocol analysis. The primary comparison between current practice and clinical pathway will be performed for patients from all hospitals participating in the PELVIC study. A secondary sensitivity analysis will be done to compare the outcomes when excluding the hospitals that are currently operating and conform a protocol very similar to the clinical pathway. Another sensitivity analysis will be done where the outcomes of the patients with an isolated ramus fracture will be excluded since the advice for treatment in the clinical pathway of this subgroup is very similar to the current practice. Missing data on baseline characteristics will be imputed by multiple imputation techniques. Outcome data will not be imputed, patients who died or are lost to follow-up within 1 year will remain in the analysis as censored at the date of loss to follow-up. Complete and multiple imputed data analyses will be performed to check for inconsistencies.

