**Protocol version:**

V.1.0, 19 July 2022

STRENGTHS AND LIMITATIONS OF THIS STUDYThe stepped-wedge design allows for the systematic implementation of multiple interventions in various aspects of the diagnosis and treatment strategy for pelvic fragility fractures, providing a holistic approach to addressing this multifactorial problem.Focusing on mobility as the primary outcome, rather than mortality, aligns with the priorities of older adult patients and demonstrates a patient-centred approach.The stepped-wedge design facilitates more targeted and coordinated visits at the participating centres, improving adherence to the protocol compared with a regular randomised controlled trial design.The stepped-wedge design introduces complexity into the statistical analysis due to the sequential introduction of clusters, making data analysis more challenging.The multifaceted approach in the stepped-wedge design makes it difficult to determine which specific intervention has the most significant impact on outcomes, hindering the identification of the most effective strategies.

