The PELVIC study is a closed cohort stepped wedge cluster randomised design, which involves a sequential crossover of clusters with the order of crossover randomly determined. This study will be conducted with a superiority design and aims for regional implementation of an evidence-based and expert opinion-based clinical pathway. The primary objective of this study is to evaluate whether the implementation of a clinical pathway can improve short-term mobility (<6 weeks) in all patients ≥50 years who sustained an FFP after low-energy trauma (LET). The secondary objectives are to assess the effect on functional performance, quality of life, return to home rate, level of pain, type and dosage of analgesic medications used, falls after hospital discharge, (fracture-related) complications, 1-year and 2-year mortality rate including (presumed) cause of death.

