### Study timeline

At the start of the study, all clusters will be in the control phase for 6 weeks. After 60 weeks, all clusters will have crossed over to the intervention phase and will remain in the intervention phase for another 6 weeks. The total duration of the trial will be 66 weeks and is determined by the number of participating centres and the required sample size. Details of the sample size calculation are described in the ‘Sample size calculation’ section. The order in which the clusters will cross over is randomised. To achieve effective implementation of the clinical pathway, a structured 2-week wash-in phase was designed. In this time frame, the study team will discuss with the local hospital how to implement the clinical pathway efficiently. It is important to avoid contamination of the data for clusters still in the control phase. Details on the clinical pathway will, therefore, not be shared with local clinicians before the transfer to the intervention phase. In the analysis of this study, every cluster is their own control because of the cluster RCT design.

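### The stated primary comparison is before versus after implementation with no adjustment for calendar time, so about 41% to 56% of a linear secular trend would be read as pathway effect

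*Protocol article*

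**What the plan says.** All references are to the protocol article.

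- Statistical methods gives the comparison: "Outcomes of all patients with an FFP will be analysed before and after the implementation of the clinical pathway". It sets exposure by calendar date: "Patients will be assigned to current practice or clinical pathway cohort based on the date of first hospital contact".
- The same section says "Primary analysis will be performed with an intention-to-treat analysis according to the randomisation order and cross-over dates" and "A two-sided p<0.05 will be taken as threshold of statistical significance in all statistical tests". The distributional checks it names are general: "Normality of continuous data will be tested with the Shapiro-Wilk test", plus Levene's test for variances.
- Study timeline says "In the analysis of this study, every cluster is their own control because of the cluster RCT design".
- The strengths and limitations list concedes that "The stepped-wedge design introduces complexity into the statistical analysis due to the sequential introduction of clusters, making data analysis more challenging", but gives no method for dealing with it.
- The Introduction states "The PELVIC study is a closed cohort stepped wedge cluster randomised design". Eligibility criteria and Statistical methods describe something else: newly presenting patients, each placed once in one condition.

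No section mentions calendar period, secular trend or a regression model. Neither Statistical methods nor Sample size mentions correlation within centres.

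**The concern.** Every centre begins under current practice and ends under the pathway. Control patients are therefore early and pathway patients late, whatever the randomised order. The random order protects the comparison only if the analysis compares exposed and unexposed centres within the same calendar period. A before/after contrast does not do that, so a background change in outcome is partly credited to the pathway, or partly masks its effect if the change is downward.

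Such change is plausible on the article's own account. The abstract speaks of recent new insights into diagnosis and minimally invasive surgery, and the Introduction says newer techniques have made surgery more accessible to older patients. At stake is whether the primary result is a randomised comparison or a pre/post one.

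The closed-cohort label adds confusion, because it suggests repeated measurement of the same people under both conditions. No patient here contributes to both.

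**Working it through.** **Inputs from the article.** Nine centres in nine sequences (Study setting); one switch every 6 weeks (Abstract); 393 patients, 197 per group, 80% power, 10% improvement (Sample size); two-sided 5% level (Statistical methods). **Assumed, because not given:** control success rate, ICC, size of drift.

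**1. The article's own figure.** The control rate is not stated, so 393 cannot be reproduced from stated inputs alone. Assuming 80% versus 90%, the unpooled two-proportion formula gives

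n = 7.849 × (0.8×0.2 + 0.9×0.1) / 0.10² = 7.849 × 0.25 / 0.01 = 196.2 per group, or 393 in total (2 × 196.2 = 392.4).

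That is the formula for two independent groups, with no allowance for centre or time. The match is consistent with a plain two-group comparison but does not prove one was intended.

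**2. How far exposure is tied to time.** Number ten 6-week periods 0 to 9, with centre k (k = 0 to 8) exposed from period k+1.
- Control cells: 45, sum of period numbers 120, mean 120/45 = 2.67.
- Pathway cells: 45, sum 405 − 120 = 285, mean 285/45 = 6.33.
- Pooled gap: 3.67 periods = 22 weeks. Share of a linear first-to-last drift: 3.67/9 = 41%.
- Within centre k: pathway mean (k+10)/2 minus control mean k/2 = 5 periods for every centre. Share: 5/9 = 56%.

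Nine switches at 6-week steps place the last at week 54 and the end at week 60, whereas Study timeline gives weeks 60 and 66. With an eleventh period the gaps are 4.28 and 5.5 periods out of 10, so the shares are 43% and 55%. The conclusion does not change.

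**3. Type I error.** Trials were simulated with no pathway effect: 393 patients, nine unequal centres, ten periods, base rate 50%, linear drift, 3,000 runs per setting (Monte Carlo standard error about 0.4 points at 5%).

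| Drift, first to last | ICC | Pooled test | Centre only | Centre + period |
|---|---|---|---|---|
| 0 | 0 | 4.4% | 5.1% | 4.6% |
| 0 | 0.05 | 13.3% | 5.6% | 5.6% |
| 5 points | 0.01 | 9.0% | 8.9% | 6.1% |
| 10 points | 0.01 | 12.8% | 14.2% | 5.3% |
| 10 points | 0.05 | 20.7% | 15.9% | 4.7% |
| 20 points | 0.01 | 37.0% | 46.8% | 5.1% |

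With a 10-point drift at ICC 0.01 the mean spurious effect was 4.0 points pooled and 5.5 points within centre, in line with step 2; with period terms it was about zero. The base rate matters: at an assumed 80%, on the eleven-period grid, the pooled test rejected in 22% (ICC 0.02) and 24% (ICC 0.05) of trials with a 10-point drift.

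**4. What period adjustment costs.** The Hussey–Hughes variance with I = 9 centres, T = 10 periods, U = 45, W = V = 285 is

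Var = Iσ²(σ² + Tτ²) / [(IU − W)σ² + (U² + ITU − TW − IV)τ²].

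Example: 80% versus 90%, ICC 0.01, 393/90 = 4.37 patients per cell. Mean rate 0.85 gives variance 0.1275, so τ² = 0.001275 and σ² = 0.99 × 0.1275/4.37 = 0.0289. Var = 0.01084 / (120 × 0.0289 + 660 × 0.001275) = 0.01084/4.311 = 0.00251, standard error 0.0501. Power = Φ(0.10/0.0501 − 1.96) = 51%; 80% power needs about 861 patients.

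| Assumed control rate | Plain two-group power, 197 per group | Centre + period, ICC 0 to 0.10 |
|---|---|---|
| 80% | 80% | 43% to 57% |
| 50% | 51% | 25% to 33% |
| 20% | 63% | 31% to 42% |

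Across these settings, 80% power needs about 680 to 2,140 patients. At 50% and 20%, part of the shortfall comes from the control rate rather than from the period adjustment.

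**The case against.** The strongest reply is that the article names no primary test or model, that a model formula is normally left to an analysis plan, and that such a plan may exist. The before/after sentence can be read as merely defining the two conditions. The article also ties exposure to the randomised order, commits to the stepped-wedge reporting extension (Study setting) and admits that the design complicates analysis, none of which suggests a deliberate choice of a naive test.

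Much of this stands, and it rules out four stronger readings.
- *That a t-test is planned.* A reader might infer this from the normality and variance checks. They are stated for continuous data in general, and the improvement defined under Sample size is a count of responders, to which neither applies.
- *That centre is ignored.* This would be inference from silence, and the own-control sentence points to a within-centre contrast. With centre in the model and no trend, the error rate is near 5%.
- *That all of any trend is absorbed.* The share is 41% to 56% of a linear one.
- *That the 5% level necessarily fails.* With no trend and no within-centre correlation it holds. The article gives no rate of change in outcomes.

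What does not stand is that these statements supply a time adjustment. The intention-to-treat sentence fixes who counts as exposed, and the complexity remark names no method. The charitable reading, a within-centre contrast, takes up more of a trend than the pooled one.

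**Conclusion.** The concern holds in a bounded form. The one comparison the article states does not suit the design, and followed as written it would give a result that the randomised order does not protect. The decisive gap is calendar time; a centre term alone does not close it. The 41% and 56% shares follow from the layout and the assumption of a linear trend. The error rates and power figures rest on assumed drift, ICC and control rate, and should be read as ranges. The simulation used a constant centre effect, with no variation of centres over time. If an analysis plan already contains a suitable model, what remains is to bring the Introduction, Study timeline and Statistical methods into line with it.

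**What to change.** In Statistical methods, state that the primary analysis is a regression matched to the primary scale, with a treatment indicator by scheduled crossover date, calendar-period effects, centre effects and pre-injury PMS as covariate. State inference suited to nine clusters: for example, permutation of the randomised order, or a small-sample correction that belongs to the chosen model (Kenward–Roger is for linear mixed models, not logistic ones). With about four patients per centre-period, centre-by-period effects would be poorly estimated, so whether to include them can be left to the analysis plan.

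In Study timeline, keep the own-control sentence but add that the comparison is also adjusted for calendar period. In the Introduction, replace the closed-cohort label with continuous recruitment and one exposure per patient.

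The wording is cheap to change. The real cost is a wider confidence interval. Recompute power under the named model with a stated control rate and ICC, and restate either the sample size or the power it provides.

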## Ethics and dissemination

The Medical Research Ethics Committee (MREC) of Academic Medical Center confirmed that the Medical Research Involving Human Subjects Act (WMO) does not apply to the above-mentioned study and that an official approval of the study is not required. Important protocol modifications will be notified to the MREC of the participating centres.

Informed consent will be obtained using the opt-out method to minimise the significant information and selection bias that will otherwise occur.

Research data will be stored in a database (eg, Castor Electronic Data Capture or a similar platform that meets Good Clinical Practice standards) and will be handled confidentially. Any information collected during this study on paper will be placed in a research folder, which will be filed in locked cabinets in research offices at the participating hospitals. Any electronic information will be saved in a password-protected area; only the study staff will have access to these data. Research data that can be traced to individual persons can only be viewed by authorised personnel.

Prior to the start of the study, the PELVIC study was registered in an online database of clinical research studies (ClinicalTrials.gov). The final study report will be shared via Open Access publication without restrictions from funding parties and regardless of the outcome.
